| CONCOMITANT MEDICATION                       | 
Allowed
 
N.A.
 
Not allowed
 
N.A.
                                                                                                                                                                                                                                                                                                                                                                                                                                                                                                                                                                                                                                                                               |
| EFFICACY ENDPOINTS                           | See primary and secondary objectives.                                                                                                                                                                                                                                                                                                                                                                                                                                                                                                                                                                                                                                                                                                                 |
| TOLERABILITY / SAFETY ENDPOINTS              | 
Surgical complications will be assessed and graded according to the latest "Clavien-Dindo Classification of surgical complications".
 
The latest National Cancer Institute (NCI) CTCAE will be used to assess any adverse effects of the drugs (Ipilimumab, Nivolumab) used in the presents study.
                                                                                                                                                                                                                                                                                                                                                                                                                                       |

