### 9.3.1 Hospitalization – Prolongation of existing hospitalization

Hospitalization is defined as an overnight stay in a hospital unit and/or emergency room. An additional overnight stay defines a prolongation of existing hospitalization.

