### **Non-serious Adverse Event Collection and Reporting**

The collection of non-serious AE information should begin following the subject's written consent to participate in the study. All non-serious adverse events (not only those deemed to be treatment-related) should be collected continuously during the treatment period and for a minimum of 100 days following the last dose of study treatment.

Non-serious AEs should be followed to resolution or stabilization, or reported as SAEs if they become serious. Follow-up is also required for non-serious AEs that cause interruption or discontinuation of study drug and for those present at the end of study treatment as appropriate.

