#### 11.4.4 Safety and tolerability endpoints

The safety analysis will be performed in all participants who have received at least 1 dose of study treatment. Descriptive statistics of safety will be presented using latest NCI CTCAE by treatment arm. Adverse events, treatment-related AEs, SAEs and treatment-related SAEs will be tabulated using worst grade per latest NCI CTCAE criteria by system organ class and preferred term. On-study lab parameters including hematology, chemistry including liver function and renal function will be summarized using worst grade per latest NCI CTCAE criteria.

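### Section 11.4.4 summarises worst CTCAE grades over a period that includes rectal surgery, which can attenuate the arm difference in laboratory values and in shared or aggregated adverse events

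*Protocol*

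**What the plan says.** The protocol synopsis, under tolerability and safety endpoints, names two instruments with separate purposes. For operative outcomes: "Surgical complications will be assessed and graded according to the latest" Clavien-Dindo classification. For the drugs: "The latest National Cancer Institute (NCI) CTCAE will be used to assess any adverse effects of the drugs (Ipilimumab, Nivolumab"). Both instruments also appear in the primary objective (section 6.1).

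Section 11.4.4 then fixes the CTCAE summaries, descriptively and by arm. Four categories are listed, "Adverse events, treatment-related AEs, SAEs and treatment-related SAEs", and these "will be tabulated using worst grade per latest NCI CTCAE criteria by system organ class and preferred term". For the laboratory: "On-study lab parameters including hematology, chemistry including liver function and renal function will be summarized using worst grade". No period is defined for either, and neither is divided at surgery.

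The collection window is long. Under section 9.6, non-serious AEs "should be collected continuously during the treatment period and for a minimum of 100 days following the last dose of study treatment". Table 4 marks both AE recording and routine laboratory tests at the surgery visit (Week 15-17) and at the end-of-study visit (Week 20). Section 9.2.2 counts an untoward event as an AE whether or not the drug caused it. Section 9.3 makes prolonged hospitalisation a criterion of seriousness, and section 9.3.1 sets the threshold: "An additional overnight stay defines a prolongation of existing hospitalization". Planned admissions are exempt there, but complications are not.

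**The concern.** A post-operative complication meets the AE definition and, with one extra night in hospital, the SAE definition. It is graded by Clavien-Dindo and also enters the all-cause CTCAE tables that the synopsis reserves for drug effects. In the same way, a peri-operative fall in haemoglobin or shift in chemistry can become a patient's worst on-study grade and displace what happened during chemoradiotherapy and the waiting period.

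The all-cause table by arm matters because it is the only randomised comparison of toxicity that does not rest on a judgement of causality. Safety and tolerability are the primary question of this trial. A comparison that carries a surgical background in both arms shows an excess from immunotherapy less clearly than the same data divided at surgery.

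**Working it through.** The protocol gives no figure of its own for this point. Its sample-size figure of 49 concerns surgical complications and plays no part here.

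**Step 1: is surgery inside the window?**

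- Last nivolumab dose: day 42 (section 8.2.3). AE collection runs at least 100 days further: 42 + 100 = day 142.
- Surgery: Week 15-17 (Table 4; section 8.3, 10-12 weeks after a 5-week course). 15 × 7 = day 105; 17 × 7 = day 119. That is 63 to 77 days after the last dose.
- Last scheduled AE and laboratory assessment: Week 20, day 140.

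Surgery and the early recovery lie wholly inside both windows.

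**Step 2: which summaries are exposed?**

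- Laboratory values: one on-study worst grade per parameter, with no attribution. Exposed wherever surgery disturbs the parameter.
- AEs and SAEs: exposed in overall and organ-class incidence, and in preferred terms that surgery and the drugs can both cause.
- Preferred terms that surgery does not cause: not exposed.

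**Step 3: size for an any-event proportion.** Let d be the pre-surgery event rate and q the post-operative rate. Assume that q is equal in both arms and independent of d. Then

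whole-period rate = 1 - (1 - d)(1 - q)

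whole-period difference = (d_T - d_C)(1 - q)

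Table 1 gives 23% (any surgical complication) and 39% (any postoperative complication). The share of the difference that remains is 1 - 0.23 = 0.77 or 1 - 0.39 = 0.61.

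Illustration, with assumed pre-surgery rates of 15% (control) and 35% (treatment), which are not in the protocol:

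| q | Control | Treatment | Difference |
|---|---|---|---|
| 0 (divided at surgery) | 15% | 35% | 20 points |
| 0.23 | 1 - 0.85 × 0.77 = 34.6% | 1 - 0.65 × 0.77 = 50.0% | 15.4 points |
| 0.39 | 1 - 0.85 × 0.61 = 48.2% | 1 - 0.65 × 0.61 = 60.4% | 12.2 points |
| 0.80 (assumed, a laboratory value that surgery disturbs in most patients) | 1 - 0.85 × 0.20 = 83% | 1 - 0.65 × 0.20 = 87% | 4 points |

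At the protocol's own rates this is attenuation. Near-complete loss needs a q of about 80%, which is plausible only for some laboratory values.

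**Step 4: what if q differs between arms?** Take q = 23% in control and the doubled 46% of section 11.2 in treatment. The rates are then 34.55% and 1 - 0.65 × 0.54 = 64.9%, a difference of 30.35 points instead of 20. The pooled table can therefore overstate as well as understate the pre-surgery difference, and it does not show which.

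**Step 5: would a plain split at surgery be fair to both arms?** Table 4 marks the visits at Weeks 9 and 12 for the treatment arm only. Scheduled on-treatment laboratory tests before the surgery visit number 9 in the treatment arm (Weeks 1-6, 9, 12, 15) and 7 in control (Weeks 1-6, 15). A worst grade over more samples tends to be higher, so an unadjusted pre-surgery comparison would be biased against the treatment arm.

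**The case against.** The strongest reply is that section 11.4.4 already separates what matters. AEs are tabulated by organ class and preferred term, treatment-related AEs and SAEs have their own tables, and surgery has its own scale. The tables are descriptive, and dividing them by period is ordinary table detail that a separate analysis plan may contain. Dates are recorded, so nothing is lost.

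Much of this stands. A reader might infer that each patient is reduced to a single worst grade and that surgery hides the difference between the arms. The text does not support that: preferred terms untouched by surgery are not diluted. A reader might also express the loss as reduced power, but no test is planned on these tables, so no power figure applies. Nor can 39% be read as an SAE rate. It counts any postoperative complication, while the SAE-level rate is not given. Assuming an equal q in both arms also presumes an answer to the surgical question in the trial's hypotheses. Finally, a patient whose operation is cancelled for toxicity cannot add surgical events, but the documents give nothing from which to size that effect.

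Two parts of the reply do not stand. The treatment-related tables are no substitute: relatedness is judged by an open-label investigator, requires that nothing else explains the event (section 9.5), and refers to drugs the control arm never receives, so there is no like-for-like control figure. Laboratory summaries carry no attribution at all. As for the analysis plan, section 11.4 does not stay silent: it states a worst-grade rule, and that rule fits poorly with the purpose given in the synopsis.

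**Conclusion.** The point holds as a limitation of the descriptive CTCAE tables. It is strongest for laboratory worst grades, and weaker for overall and organ-class incidence and for terms that surgery and the drugs share. Under an equal and independent post-operative rate, 77% or 61% of an any-event difference would remain at the protocol's 23% and 39%. Those two rates serve as stand-ins only, since neither is specific to CTCAE grades or SAEs. With unequal rates the direction can reverse.

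A reader might go further and call the synopsis and section 11.4.4 contradictory. They are not: the related-event tables serve the synopsis purpose in part, and the primary objective covers the whole regimen including resection. The right label is a cheap improvement to the CTCAE part of the primary objective.

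**What to change.** In section 11.4.4, define the on-study period and add tables by arm of AEs, SAEs and worst laboratory grade for two periods: (a) randomisation to the day before surgery, or to the last assessment if no surgery takes place; and (b) surgery to the last assessment. Keep the whole-period table alongside with equal standing, so that post-surgery events, which the protocol deliberately collects, are not demoted.

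For the laboratory comparison in period (a), use only the visits scheduled in both arms, and list the Week 9 and Week 12 results of the treatment arm separately.

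The cost is a few sentences and more tables. AE start and end dates (section 9.6) and procedure dates (section 8.7.1) are already recorded, so no visit, sample or treatment changes. The price of the visit restriction is that the between-arm laboratory comparison leaves out the Week 9 and Week 12 values.

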| PHARMACOKINETIC / PHARMACODYNAMIC ENDPOINTS  | N.A.                                                                                                                                                                                                                                                                                                                                                                                                                                                                                                                                                                                                                                                                                                                                                  |
| QUALITY OF LIFE / PHARMACOECONOMIC ENDPOINTS | Quality of life will be assessed by the latest version of the European Organization for Research and Treatment of Cancer (EORTC) Quality of Life Group (QLG) questionnaires C30 and CR29.                                                                                                                                                                                                                                                                                                                                                                                                                                                                                                                                                             |
| STATISTICAL METHODOLOGY                      | 
Primary Endpoint
 
Safety, tolerability and feasibility of standard neoadjuvant CRT with sequential ipilimumab and nivolumab following surgical resection.
                                                                                                                                                                                                                                                                                                                                                                                                                                                                                                                                                                         |

[figure not shown]

Safety and tolerability will be represented by published values of known complications of CRT following surgery (Table 1).

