| 13.1   | Informed consent of subjects            | 45 |
| 13.2   | Acknowledgement / approval of the study | 45 |
| 13.2.1 | Changes in the conduct of the study     | 45 |
| 13.3   | Insurance                               | 46 |
| 13.4   | Confidentiality                         | 46 |
| 13.5   | Ethics and good clinical practice (GCP) | 46 |
| 14     | REFERENCES                              | 47 |

[figure not shown]

Table 4. Visit and assessment schedule.

| PERIODS                        | Name     | SCREENING     | TREATMENT     |           |           |           |           |           |           |           |           |           |            | FOLLOW-UP |
|--------------------------------|----------|---------------|---------------|-----------|-----------|-----------|-----------|-----------|-----------|-----------|-----------|-----------|------------|-----------|
|                                | Duration | 3 weeks       | 17 weeks      |           |           |           |           |           |           |           |           |           |            | 3 weeks   |
| VISITS                         | Number   | 1             | 2             | 3         | 4         | 5         | 6         | 7         | 8         | 9*        | 10*       | 11        | 12         | 13        |
|                                | Name     | Screening     | Randomization | Control 1 | Control 2 | Control 3 | Control 4 | Control 5 | Control 6 | Control 7 | Control 8 | Control 9 | Control 10 | EOS       |
|                                | Time     | Day -21 to -1 | Day 0         | Week 1    | Week 2    | Week 3    | Week 4    | Week 5    | Week 6    | Week 9    | Week 12   | Week 15   | Week 15-17 | Week 20   |
| Informed Consent               |          | X             |               |           |           |           |           |           |           |           |           |           |            |           |
| Inclusion / Exclusion Criteria |          | X             |               |           |           |           |           |           |           |           |           |           |            |           |
| Medical History                |          | X             |               |           |           |           |           |           |           |           |           |           |            |           |

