### 7.1.5 Study duration

The study duration for the individual participant will be approximately 20 weeks: 5 weeks of standard neoadjuvant CRT, following surgery 10 to 12 weeks after, including routine clinical and diagnostic work up of about 3 weeks.

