### 8.2.3 Dosage and administration

**Initial dose:** Ipilimumab 1 mg/kg on day 7 during standard neoadjuvant CRT

**Maintenance dose:** N.A.

**Route of administration:** IV over 30 minutes

**Duration:** single dose

**Initial dose:** Nivolumab 3 mg/kg on day 14 during standard neoadjuvant CRT

**Maintenance dose:** 3 mg/kg

**Route of administration:** IV over 30 minutes

**Duration:** given every 2 weeks until day 42 (3 cycles in total)

**Initial dose:** Capecitabine 1650 mg/m^2/d given as two equal doses per day concurrent with standard neoadjuvant CRT

**Maintenance dose:** 1650 mg/m^2/d given as two equal doses per day

**Route of administration:** PO

**Duration:** given concurrent with standard neoadjuvant CRT over 25 working days

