## 8.3 Surgery

Patients will be operated about 10-12 weeks post CRT. Surgical options included standard total mesorectal excision (TME) or extended TME (*i.e.* TME with adjacent visceral resection) with or without sphincter preservation (abdominoperineal excision; APE) according to a standardized technique [34][3]. Patients will receive either a minimal invasive (laparoscopic, laparoscopic-assisted or robotic) or an open approach, depending on the perioperative circumstances (*i.e.* body constitution and cardiopulmonary fitness of the patient) and the surgeon's choice and expertise.

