### 8.7.8 End-of-study (EOS) examination

After successful surgery (approximately 20 weeks after treatment period) patients undergo the EOS examination, which entails a standard patient visit according to routine surgical practice.

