#### 11.4.3 Secondary endpoint analysis

Statistical analysis of secondary objectives, especially between control and treatment arm will be performed according the nature of the outcome parameter. Nominal and dichotomous, outcomes will be compared by Chi-squared or Fisher's exact tests, continuous variables will be compared by T-tests (after  $\log_2$  transformation) or by Mann-Whitney-U tests and censored survival outcomes by Cox-regression analysis. Potential confounders will be considered in corresponding statistical models. Multiple testing will be corrected for by the Holm's Step-Down method or by the false discovery rate (FDR) method after Benjamini-Hochberg (especially omics data) [42]. Adjusted p-values (q-values) below 0.05 will be considered as statistically significant.

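### The EORTC quality-of-life questionnaire is scheduled only at Weeks 2, 4, 6 and 15, so there is no pre-treatment score to measure change from or adjust for, and no score after surgery

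*Protocol*

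**What the plan says.** The synopsis (section 2), in its row for quality-of-life and pharmacoeconomic endpoints, states "Quality of life will be assessed by the latest version of the European Organization for Research and Treatment of Cancer (EORTC") and names the C30 and CR29 modules. The only place that says when they are completed is the visit schedule printed after the table of contents ("Table 4. Visit and assessment schedule"). Its questionnaire row is marked at visits 4, 6, 8 and 11, which are Weeks 2, 4, 6 and 15. The cells for screening, Day 0, Week 1, the surgery visit (Week 15-17) and the end-of-study (EOS) visit (Week 20) are blank.

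Treatment timing comes from section 8.2.3: "Ipilimumab 1 mg/kg on day 7 during standard neoadjuvant CRT" and "Nivolumab 3 mg/kg on day 14 during standard neoadjuvant CRT", the latter repeated every two weeks to day 42. Section 7.1.5 gives "5 weeks of standard neoadjuvant CRT, following surgery 10 to 12 weeks after", and section 8.3 agrees: "Patients will be operated about 10-12 weeks post CRT". Section 8.7.8 describes the visit after surgery: "patients undergo the EOS examination, which entails a standard patient visit according to routine surgical practice".

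For secondary outcomes, section 11.4.3 says that "continuous variables will be compared by T-tests" after a log transformation, or by Mann-Whitney tests, with potential confounders considered. Section 11.4.5 allows baseline parameters into the analyses of secondary objectives where appropriate. Quality of life is not among the objectives listed in section 6.2.

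**The concern.** A quality-of-life endpoint is normally read in two ways: how far each patient moved from where they started, and whether the arms differ at later visits once the starting score is taken into account. Both need a score from before treatment, and in an open-label trial preferably from before the patient knows the allocation. This schedule collects none. By the first questionnaire all patients have started CRT and know their arm, and those in the treatment arm have had ipilimumab.

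Using Week 2 as a substitute baseline would not repair this. Any effect of ipilimumab during its first week, or of knowing the allocation, would already be in that score, and adjusting for it would remove part of the effect of interest.

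The schedule also stops before the operation, although every patient is planned to have surgery and a visit already exists afterwards. An analysis plan written later cannot recover scores that were never collected, so this has to be settled in the protocol.

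**Working it through.** **1. Reading the schedule.** Each row of Table 4 was set against its 13 time points. To make sure that columns had not shifted in the extracted text, rows whose timing is also stated elsewhere were checked first:

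| Row | Marks in Table 4 | Timing in the text |
|---|---|---|
| Ipilimumab | Week 1 | day 7 (8.2.3) |
| Nivolumab | Weeks 2, 4, 6 | day 14, every 2 weeks to day 42 (8.2.3) |
| Tumor biopsy | screening, Weeks 2, 4 | pre-treatment, days 14, 28 (8.7.5) |
| Liquid biopsy | screening, Weeks 1, 2, 4, 6, surgery visit, EOS | screening, days 7, 14, 28, 42, before surgery, EOS (8.7.6) |

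All agree, so the questionnaire row can be trusted: Weeks 2, 4, 6 and 15.

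**2. Position of the first score.**
- Randomization is on Day 0 (section 8.4), so the first score is 14 days later.
- Ipilimumab is on day 7: 14 - 7 = 7 days before the first score.
- Surgery at Weeks 15-17, less 10-12 weeks, puts the end of CRT at Week 5. Less 5 weeks of CRT, its start is at Week 0. On that reading about 2 x 5 = 10 of the 25 fractions precede the first score.
- If CRT is instead taken to start only at Week 1, where Table 4 first marks it, the first score is still about one week into CRT.

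On either reading there are no pre-treatment scores.

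**3. Position of the last score.** Visit 11 (Week 15, with the restaging pelvic MRI) precedes visit 12 (surgery, Week 15-17). There are no post-operative scores. The EOS visit at Week 20 falls 20 - 17 = 3 to 20 - 15 = 5 weeks after surgery and has no questionnaire.

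**4. What the missing baseline costs in precision.** The protocol gives no SD or correlation for these scales, so the following are assumptions: SD 20 points on a 0-100 scale, correlation r between baseline and follow-up of 0.5 to 0.7, and complete questionnaires in arms of 50 and 30.

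Unadjusted standard error of the difference between arms:
SE = SD x sqrt(1/50 + 1/30) = 20 x 0.2309 = 4.62 points.

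Adjusted for a baseline score: SE x sqrt(1 - r^2).
- r = 0.5: 4.62 x 0.866 = 4.00, a reduction of 1 - 0.866 = 13%.
- r = 0.7: 4.62 x 0.714 = 3.30, a reduction of 1 - 0.714 = 29%.

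With SD 25 the unadjusted figure is 25 x 0.2309 = 5.77. The percentage reductions are the same, because they depend only on r.

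**The case against.** The best defence is that little in the protocol depends on this endpoint. Quality of life appears in one synopsis row and one row of Table 4. It is not a primary or secondary objective in section 6 and has no hypothesis, decision rule or role in the sample size. The protocol nowhere promises an analysis of change from baseline, so the schedule does not contradict a stated analysis. All of this stands and limits the weight of the point.

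Three stronger readings are tempting and are not supported.

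- A reader might infer that the comparison between arms is biased, or that chance imbalance at baseline is a further error on top of the usual one. Neither holds. Randomization keeps the comparison at Weeks 2 to 15 unbiased by baseline differences, and chance imbalance is already contained in its standard error.
- A reader might infer that the regimen under test has no quality-of-life outcome. The Week 15 score follows every planned dose of CRT, ipilimumab and nivolumab, so the completed neoadjuvant part is captured. What is missing is the period after surgery, which both arms undergo.
- A reader might infer that tolerability of the whole sequence goes unmeasured. Sections 6.1 and 8.7.3 assess it by CTCAE and Clavien-Dindo, and Table 4 records adverse events from Day 0 through EOS. Only the patient-reported view after surgery is absent.

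It can also be said that a score 3 to 5 weeks after surgery reflects early recovery, and that wanting it is a matter of preference. That is fair, so the EOS questionnaire is proposed only as an option.

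**Conclusion.** The point holds as a gap in the assessment schedule. The listed quality-of-life endpoint has no score from before treatment or allocation and none after surgery. Three things are lost: within-patient change for every patient, precision in the comparison of arms, and post-operative quality of life.

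The precision loss is the only part that can be sized. Under the assumed SD of 20 and correlation of 0.5 to 0.7, the standard error is 4.6 points where 4.0 to 3.3 could be had. The schedule facts rest on the protocol alone; the precision figures rest on assumptions that the protocol does not supply.

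The primary safety analysis and the reoperation stopping rule are untouched. This is an inexpensive improvement to a supporting endpoint, not a threat to the trial's main conclusion.

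**What to change.** In the questionnaire row of Table 4, add C30 and CR29 at the existing screening visit, completed after consent and before randomization. Keep the Week 2 questionnaire: it is the only score between ipilimumab and the later visits, and moving it to screening would give up an early on-treatment assessment. State in section 11.4 that the arms will be compared on the later scores adjusted for the screening score.

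Optionally, add the questionnaire at the existing EOS visit (Week 20) to capture early post-operative quality of life.

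The cost is one or two extra questionnaires per patient, a few minutes each, at visits that already take place. No new visit and no change to sample size or treatment is needed. For patients already enrolled when the change takes effect, a missed screening score cannot be recovered, so the gain is larger the earlier it is made.
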